It is well established that any type of surgery is a form of trauma for human beings, regardless of the size of the trauma, but it is also likely to cause damage, and some such damage is even harmful. Despite many advantages of OLIF in lumbar spine surgery, it is also an invasive operation for the body, which may lead to residual symptoms or new complications in some patients after surgery and may indirectly increase the rate of lumbar reoperation and reduce the effect of surgery [18]. Therefore, it is imperative to adopt other means after lumbar surgery to reduce residual symptoms and postoperative complications. The commonly used clinical approaches include prolonged bed rest after surgery, avoidance of labor, lifting heavy articles, and prolonged standing or sitting and wearing a spinal orthosis. A better and commonly used clinical method to avoid reducing the quality of life of patients after surgery is to wear a spinal orthosis routinely after surgery.

Generally, fixation of any musculoskeletal injury is favorable for reducing the pain after injury [19]. Therefore, spinal orthoses can be used not only to relieve residual back pain symptoms [20] but also for postoperative rehabilitation of patients after lumbar spine surgery [21]. The use of spinal orthosis after OLIF is to fix the entire body movement [22] and the motion segment, relieve muscle strength [23], reduce pain [24], enhance the fusion rate [25], and improve the functional prognosis [26]. However, it is undeniable that non-standard or the wearing of spinal orthoses not for the prescribed time after surgery may also lead to muscle atrophy [27], skin irritation, delayed recovery, and other side effects.

For this reason, although the spinal orthosis exhibits some advantages after lumbar fusion, the necessity of its clinical use has been questioned due to its limitations. Additionally, the role of postoperative orthoses in OLIF has not been determined, and there is a lack of strong evidence to prove any correlation between the routine use of orthoses after OLIF and the final clinical outcome of patients. Therefore, we plan to conduct a randomized trial to evaluate the necessity of using lumbar orthoses after OLIF for postoperative adjuvant therapy in such patients.

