### Assumption

It is assumed that the clinical outcome of patients wearing spinal orthoses after OLIF is superior to that of patients in the control group.

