## Methods/design

This is a randomized controlled trial, with the aim of comparing the effects of spinal orthosis on the clinical outcomes of patients after OLIF. This study was approved by the Ethics Committee of the Fourth Clinical Medical School of Xinjiang Medical University and will be conducted in accordance with the *World Medical Association Declaration of Helsinki*. This study has been registered in the Chinese Clinical Trial Registry (Registration No.: ChiCTR2200059000). Before treatment, all patients should sign the informed consent form.

The evaluation and statistical analysis of the results of this study will be performed by professionals who are not involved in the grouping. The study flow is shown in Fig. 1. The patients will be randomized into two groups, that is, group A (those wearing spinal orthoses after surgery) and group B (those not wearing spinal orthoses after surgery; control group).

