### Randomization and blinding

Physicians [name] and [name], from the Fourth Affiliated Hospital of Xinjiang Medical University, will use computer software to generate random sequences, which will be sealed in envelopes. Eligible patients will be recruited by physicians of the department, [name] and [name]. The recruited patients will be randomized into two groups by [name], a physician of the department. In order to avoid the predictability of random sequences, the envelopes used are all of the same kind of envelope produced by the same manufacturer (that is, the appearance, thickness, texture are the same), and all sequences are not disclosed to recruiters and allocations. In this study, a single-blind approach will be adopted, that is, participants do not know which treatment they are receiving. The specific procedures performed will be kept confidential to all participants until unblinded.

To ensure the scientific accuracy of the study, it is also planned to charge the same fee for all subjects. The specific charges are as follows: preoperative preparation fee, surgery fee, anesthesia fee, cost of related equipment used during operation, and cost of intraoperative and postoperative drugs. In particular, the spinal orthoses used by the patients in the experimental group will be uniformly distributed by the research team to ensure that the spinal orthoses used by the patients in the experimental group are the same; thus, the cost of spinal orthoses will not be included. The total cost is RMB 55969.32.

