Other treatment methods allowed in the control and experimental groups are as follows. (1) Both groups of patients can receive routine nursing treatment in the Second Spine Department of Xinjiang Uygur Autonomous Region Hospital of Traditional Chinese Medicine, including daily inquiries about the patient’s condition, pain improvement, and patient care. All nursing programs will be performed by the designated nurses of the Second Spine Department. (2) The acupuncture treatment for patients in the two groups after OLIF will be performed by the designated physician of the acupuncture department of the hospital. Additionally, the lumbar standardized acupuncture treatment is adopted, that is, all subjects have the same acupuncture treatment. (3) Traditional Chinese medicine treatment is also allowed as adjuvant therapy, and the patients in both groups receive the same treatment. Therefore, an effect of the above treatment on the overall trial results can be avoided. Other treatment methods prohibited for the control and experimental groups are as follows. (1) It is prohibited to perform other invasive treatments on the lumbar spine. (2) Subjects are prohibited from taking medications that can improve the related clinical symptoms. (3) No additional treatment may be given to patients included in the study without the consent of the investigator.

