### Dropout or loss to follow-up

All patients have the right to withdraw from the study at any time. If a patient chooses to withdraw from the study, we will revoke the patient’s consent and terminate the study participation. The chief investigator may also terminate a subject’s participation if the subject violates the rules of management for this study or has a serious adverse event. Data of these subjects will be excluded in the final analysis.

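### Subjects whom the chief investigator terminates for a rule violation or a serious adverse event are dropped from the final analysis, a discretionary post-randomisation exclusion that may depend on arm and outcome

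*Protocol article*

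**What the plan says.** The protocol article, Dropout or loss to follow-up, gives the chief investigator an option to end participation "if the subject violates the rules of management for this study or has a serious adverse event". The section closes with "Data of these subjects will be excluded in the final analysis". That sentence also covers subjects who withdraw voluntarily; this point concerns only those whom the investigator terminates.

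The rules themselves are not listed there. The nearest candidates are:

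- Monitoring, safety, and quality control: "It is prohibited to perform other invasive treatments on the lumbar spine" and "Subjects are prohibited from taking medications that can improve the related clinical symptoms". Both apply to both groups.
- OLIF surgical technique: group A is to wear the orthosis except when bathing or in bed. Group B has no matching duty.

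On blinding, Randomization and blinding says "a single-blind approach will be adopted, that is, participants do not know which treatment they are receiving", and Methods/design says "The evaluation and statistical analysis of the results of this study will be performed by professionals who are not involved in the grouping". Neither statement covers the chief investigator's decision to terminate. No section of the article keeps terminated subjects in an as-randomised analysis.

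**The concern.** Randomisation protects the comparison only while subjects stay in the groups to which they were allocated. Here, subjects can be removed afterwards for events that may follow from the allocation or signal a poor course.

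- **Serious adverse events and re-treatment.** Background says that residual symptoms or new complications "may indirectly increase the rate of lumbar reoperation and reduce the effect of surgery". It expects an orthosis to reduce pain and promote fusion, but also lists harms from improper wear. The Assumption section states: "It is assumed that the clinical outcome of patients wearing spinal orthoses after OLIF is superior to that of patients in the control group". On that reasoning such events could be more frequent in group B, although the harms listed leave the opposite possible.
- **Symptom-relieving medication.** Patients in more pain are more likely to break this rule.
- **Orthosis wear.** Only group A can breach this instruction.

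Removing poor courses generally flatters the arm that loses more of them. The planned chi-square comparison of adverse events (Statistical analysis) is also exposed: if the final analysis includes it, subjects terminated for serious adverse events would be missing from the count that should contain them.

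**Working it through.** The plan gives no figure for this rule and no rate of violations, re-treatment or serious adverse events, so there is nothing to reproduce. The check is an illustration with assumed counts.

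**Inputs.** 30 per group (Sample size). Outcome: share with a BSF score of at least 3, the best category in Table 5. The article does not name this as the between-group comparison; it is used because it is easy to follow. Assumed: r = number removed in an arm, p = fused share among the others, q = share of the removed subjects who would be found fused later if followed.

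**Formula.** Share after exclusion = p. Share if kept = [p(30 − r) + qr]/30. For A minus B, exclusion changes the difference by [(pA − q)rA − (pB − q)rB]/30.

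**Illustration: 1 removed in A, 4 in B; fused among the others 26/29 and 22/26.**

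| Handling | A | B | A − B (points) |
|---|---|---|---|
| Excluded | 26/29 = 89.7% | 22/26 = 84.6% | 5.0 |
| Kept, none fuse later | 26/30 = 86.7% | 22/30 = 73.3% | 13.3 |
| Kept, half fuse later | 26.5/30 = 88.3% | 24/30 = 80.0% | 8.3 |
| Kept, all fuse later | 27/30 = 90.0% | 26/30 = 86.7% | 3.3 |

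Exclusion therefore shifts the difference by −8.3, −3.3 or +1.7 points. The sign depends on how the removed subjects would have fared.

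**Reverse direction: 4 in A, 1 in B.** With the same fused share of 85% among the others in both arms, exclusion shows a difference of 0. If the removed subjects are kept and none fuse later, the true contrast is 0.85 × 26/30 − 0.85 × 29/30 = −8.5 points, so exclusion moves the result 8.5 points towards A.

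**Equal removals: 2 in each arm; 25/28 and 24/28.** Excluded: 89.3% − 85.7% = 3.6 points. Kept: 25/30 − 24/30 = 3.3 points if none fuse later, and 27/30 − 26/30 = 3.3 if all do. The shift is about 0.2 points.

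**VAS.** If removed subjects score d points worse than the rest, exclusion changes A minus B by (rB − rA)d/30. For 1 v 4 and d = 2 to 3 (assumed), that is 3 × 2/30 = 0.20 to 3 × 3/30 = 0.30 points, towards B. For 2 v 2 it is 0. Sample size plans on D = 0.64 without stating its unit, so no direct comparison is made.

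**Plausibility of the counts.** Five removals are half of the ten-subject allowance in Sample size (60 − 50), but that allowance covers all causes of loss.

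**The case against.** **Re-treatment is not named.** A reader might infer that the plan expressly removes re-treated subjects. It does not. The link runs through a prohibition listed in another section, which is addressed to whoever treats rather than to the subject, or through the serious adverse event ground. The rules are undefined and termination is optional. This stands, which is why the point is the stated rule as a whole, with re-treatment as one possible trigger.

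**Arm dependence is inferred.** Background attributes reoperation to residual symptoms or complications of an invasive procedure, not to the absence of an orthosis, and the Assumption section does not mention reoperation. This stands; the dependence is possible, not shown. The wear instruction, however, differs by arm by design.

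**The direction may be harmless to the claim.** A reader might infer that the rule manufactures an orthosis benefit. The documents do not support that: if group B has more poor courses, as the trial's own assumption would suggest, exclusion tends to hide benefit. A biased answer against the orthosis is still a wrong answer.

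**The counts are assumed.** Four of 30 (13%) in one arm is a lot for single-level surgery with four-screw fixation in patients without osteoporosis or previous spinal surgery. This stands.

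**Silence on the investigator's blinding may only be condensation.** That is fair, and the article does not say that the investigator is unblinded. But a blind decision would not cure the problem, because the triggering events may themselves depend on arm.

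**An unseen analysis plan might differ.** The exclusion is stated outright in the article, so it is not a detail left for later.

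**Conclusion.** The point holds for the rule as written: a discretionary exclusion after randomisation, for events that may depend on arm and outcome, with nothing in the article that keeps these subjects in. It should be changed; confidence is medium because its practical effect cannot be sized from the document. In the assumed 1 v 4 case exclusion shifts the BSF difference by between −8.3 and +1.7 points, and in the reverse case the shift can run towards group A. If removals are equal between arms, or removed subjects end up like the others, the effect is close to zero.

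The loss of serious adverse event cases from the safety comparison is conditional on the final analysis including that comparison, which the article does not say.

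**What to change.** For terminated subjects, replace the last sentence of Dropout or loss to follow-up with:

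> *Subjects with a rule violation, re-treatment or serious adverse event stay in the analysis in their allocated group. Study treatment may be stopped, but follow-up at the Table 4 visits continues unless consent is withdrawn.*

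Three changes go with it:

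- Monitoring, safety, and quality control provides for discontinuation when an adverse event is judged to be caused by the intervention. State that this means stopping the orthosis or study treatment, not follow-up; otherwise that section would still end data collection.
- Count all serious adverse events in the chi-square comparison, and report re-treatment by arm descriptively.
- If a sensitivity analysis grades re-treated subjects as *Ineffective*, do it separately for ODI, VAS and BSF, because Table 5 has separate cut-offs and no combined grade. It need not be the main comparison.

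Whether re-treatment is clinically permitted remains for the investigators.

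Cost: rewording in two sections and a short descriptive report. The visits are already scheduled in Table 4, but subjects who would have stopped now attend them, so some visits and assessments are added. Any gain from re-treatment is credited to the allocated arm, which the descriptive count reveals but does not remove.

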### Statistical analysis

The Epidtat3.0 software is adopted to enter the observation data by two members of the research group alone, and SPSS18.0 is applied for statistical analysis. Demographic and clinical characteristics (such as gender, age, and weight) of all subjects will be processed based on descriptive analysis. Quantitative data will be expressed as the mean, standard deviation, median, and range and qualitative data will be presented as frequencies and percentages. Chi-square test will be used to compare the incidence of related adverse events between the two groups.

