### Sample size

Because this study is based on clinical application, it is difficult to calculate the sample size through pre-experiments according to the actual situation; thus, the sample size of this study was finally determined based on the previous relevant literature data. The sample size outcome effect size was obtained from the literature using the ODI and VAS scores [29]. The mean change of the ODI in group A was approximately 92%, and the mean change of the VAS was approximately 0–3 points, while the mean change of the ODI in group B was approximately 85%, and the mean change of the NRS was approximately 4–5 points. The sample size was calculated using the sample size formula of the quantitative equivalence experiment *n* = 2(*Z*_*α*_ + *Z*_*β*_)^2^*δ*^2^/(*D* − *Δ*)^2^, assuming that *α* = 0.05 and *D* = 2.09 − 1.45 = 0.64, *δ*^2^ = [(0.56 + 0.78)/2]^2^ = 0.46 was obtained from literature retrieval, different values of *β* and superiority bounds were selected to calculate the sample size matrix, as shown in Table 1, and finally *n* = 50 was selected; taking into consideration a 20% dropout, thus 30 cases should be enrolled to each group, a total of 60 cases in two groups.

**Table 1 Tab1:** Sample size matrix

*α*	*β*	*D*	*δ*^*2*^	*Δ*	*n*
0.05	0.2	0.64	0.46	0.2	38
0.05	0.2	0.64	0.46	0.3	63
0.05	0.1	0.64	0.46	0.2	50
0.05	0.1	0.64	0.46	0.3	84

This trial is to be conducted in the Second Spine Department of the Fourth Clinical Medical School of Xinjiang Medical University, and hospitalized patients who meet the inclusion criteria will be included in the study. Because of the large number of patients undergoing OLIF in this department, it is possible to recruit sufficient subjects within the prescribed time; thus, an insufficient sample size is highly unlikely. In addition, there are benefits for patients participating in the study to supplement the sample size (e.g., free professional consultation, postoperative functional exercise instruction, and postoperative care consultation).

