### Monitoring, safety, and quality control

During the follow-up period, paper case report forms will be used to collect data. All data collection will be monitored in strict accordance with the standard procedures of the clinical trial center to ensure full compliance with International Coordinating Council standards and Good Clinical Practice principles. Any adverse events that occur in patients during the study period, such as worsening of clinical symptoms or loss of daily activity, will be fully evaluated through a doctor’s inquiry, physical examination, and imaging studies, and if adverse events are considered to be caused by intervention measures, the study will be discontinued and the patient will be treated symptomatically. Relevant data about the adverse events and the intervention measures in this study will be analyzed to improve the research measures. All adverse events will also be reported to the investigators. Due to short study period and low risk, we will not set up a trial steering committee. Any unexpected event will be reported directly to the investigator for comment. There is no interim analysis in this protocol, and [name] has the right to make the final decision on whether to terminate the trial.

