## Discussion

According to previous studies and clinical experience, spinal orthosis is commonly used after open lumbar fusion. However, as previously reported, there is insufficient evidence to systematically prove the necessity of using spinal orthoses after lumbar spine surgery [32]. Obviously, there is a clear lack of consensus on the indications for routine spinal orthosis use after lumbar spine surgery.

For lumbar fusion, the benefits of postoperative bracing are intensively debated. In clinical practice, due to the absence of scientific guidelines, some physicians often subjectively choose whether to use a spinal orthosis after OLIF surgery based on their own experience. This subjectivity may increase the possibility of some unnecessary risks, indirectly leading to undesirable outcomes and increasing uncertainty about prognosis, and may also increase the pain and economic burden of patients.

Patients who use spinal orthoses after surgery may feel more comfortable and, thus, move more easily under ordinary circumstances. However, there are no definitive findings on whether routine spinal orthosis use after surgery leads to any negative effects and thus adversely affects the final outcome. Accordingly, we have designed this study to prove whether routine spinal orthosis use in patients after OLIF has an impact on their clinical outcomes, so as to provide a more scientific basis for clinicians on deciding on its use.

Clearly, this study has some limitations. The clinical outcome evaluation indexes are relatively single, and the follow-up time is relatively long, which may lead to problems such as a reduced reliability of some data. Therefore, the data are collected in strict accordance with the requirements during the study, and the relevant factors affecting the experimental data are minimized and the existing limitations will be further improved in the future research process.

To our knowledge, this study is the first prospective randomized trial to evaluate the effect of spinal orthosis on postoperative clinical outcomes in patients undergoing OLIF, thus providing clinicians and patients with a more scientific treatment choice.

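### The adverse-event comparison rests on an unconditional chi-square test in 30 versus 30 patients, which gives a p-value but does not show how imprecise the comparison is

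*Protocol article*

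**What the plan says.** The Statistical analysis section of the protocol article states: "Chi-square test will be used to compare the incidence of related adverse events between the two groups". It does not say whether a continuity correction applies or what happens when counts are small. It also plans frequencies and percentages for qualitative data. The section on monitoring, safety and quality control adds a loosely worded intention to analyse adverse-event data, without a method.

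The group size comes from the Sample size section: "thus 30 cases should be enrolled to each group, a total of 60 cases in two groups", reached by "taking into consideration a 20% dropout".

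The section on dropout or loss to follow-up bears on the denominator. Participation may be ended for a patient who breaks the study rules "or has a serious adverse event. Data of these subjects will be excluded in the final analysis". No exception is made for the safety table.

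No adverse-event rate, power or precision for the safety comparison appears anywhere. The type of event is drawn broadly: "Any adverse events that occur in patients during the study period, such as worsening of clinical symptoms or loss of daily activity".

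**The concern.** Harm from the orthosis is part of what the trial could inform. The Background lists muscle atrophy, skin irritation and delayed recovery as possible effects, and the Discussion says that "there are no definitive findings on whether routine spinal orthosis use after surgery leads to any negative effects".

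With 30 per group, a large-sample test on sparse counts can turn on a single patient or on which version of the test the analyst runs. A bare p-value also gives the reader no sense of how large a difference in harm remains compatible with the data. If patients whose participation ended for a serious adverse event leave the analysis, the counts being compared may also lose the events that matter most.

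**Working it through.** **Inputs.** From the Sample size section: 30 per group; 20% dropout, so 30 × 0.8 = 24; α = 0.05. That α is stated for the efficacy calculation and is assumed here, two-sided, for the safety test. Event rates are not given; I assume a range of 2% to 40%.

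**The plan's own figure.** There is none for safety, so only the sample-size row can be reproduced. n = 2(Zα + Zβ)²δ²/(D − Δ)² = 2(1.960 + 1.282)² × 0.46/(0.64 − 0.2)² = 49.9, which matches the 50 in Table 1. This confirms that α was used two-sided. How 50 became 30 per group is a separate matter; the check below takes the stated 30 versus 30.

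**Step 1: when expected counts fall below 5.** With equal groups, the expected event count per group is total events/2, so it is below 5 when the total is 9 or fewer. Ten events in 60 patients is 16.7%; ten in 48 is 20.8%. Probability of 9 or fewer events in total, by true common rate:

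| Rate | 30 per group | 24 per group |
|---|---|---|
| 5% | 99.9% | about 100% |
| 10% | 92.7% | 98.1% |
| 15% | 58.8% | 82.6% |
| 20% | 21.3% | 50.0% |
| 25% | 4.5% | 20.5% |
| 30% | 0.6% | 5.7% |

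**Step 2: borderline tables, 30 versus 30.** Pearson X² = N(ad − bc)²/(product of the four margins).
- 3 versus 0: 60 × 90²/(30 × 30 × 3 × 57) = 3.16, p = 0.076.
- 4 versus 0: 60 × 120²/(30 × 30 × 4 × 56) = 4.29, p = 0.038.
- 6 versus 1: 60 × 150²/(30 × 30 × 7 × 53) = 4.04, p = 0.044.

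Yates subtracts N/2 = 30 from |ad − bc|. For 4 versus 0 this gives 60 × 90²/201,600 = 2.41. Fisher for 4 versus 0 is 2 × C(30,4)/C(60,4) = 2 × 27,405/487,635 = 0.112.

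| Table | Pearson | Yates | Fisher | Mid-p | Boschloo |
|---|---|---|---|---|---|
| 4 vs 0 | 0.038 | 0.121 | 0.112 | 0.056 | 0.070 |
| 6 vs 1 | 0.044 | 0.108 | 0.103 | 0.057 | 0.056 |

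**Step 3: overall size of uncorrected Pearson.** Summing binomial probabilities over all rejecting tables at 30 per group gives 0.3% at a 2% rate, 2.8% at 5%, 5.4% at 10% and 4.9% at 20%. The maximum is about 5.5% (6.0% at 24 per group).

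**Step 4: power of uncorrected Pearson, by the same enumeration.**

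| True rates | 30 per group | 24 per group |
|---|---|---|
| 5% vs 10% | 11% | 8% |
| 5% vs 15% | 26% | 20% |
| 10% vs 20% | 19% | 17% |
| 10% vs 30% | 50% | 43% |
| 10% vs 40% | 80% | 71% |

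**Step 5: what an interval would show.** Newcombe 95% intervals for the risk difference at 30 versus 30, in percentage points: 0 vs 0, −11 to +11; 3 vs 3, −17 to +17; 4 vs 0, −0.6 to +30.

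**The case against.** The strongest reply is that the chi-square test is not materially invalid here, and that is right. Step 3 shows an overall size at or just above 5%, and well below it for rare events. A reader might infer a false-positive problem from the rates conditional on 4, 7 or 10 total events (11.2%, 10.3%, 8.0%), but those are local peaks. At 5, 6, 8 and 9 events they are 5.2%, 2.4%, 5.2% and 2.6%, and at 1 to 3 events zero. At 10 events the expected count is also exactly 5, not below it.

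The article does not say that the test is uncorrected. With the continuity correction, the verdicts in Step 2 agree with Fisher. This stands, but it also shows that the stated rule leaves the verdict on such tables open.

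A reader might also infer that expected counts will usually be below 5, or that a non-significant result will be reported as safety. The documents support neither. No event rate is given, and the broad event description could take the rate to 20% or more. Nothing in the article says how p > 0.05 will be read; the Discussion sentence on negative effects describes existing evidence. Nor is the chi-square test the only safety analysis: frequencies and percentages are planned too. It is the only between-group comparison of adverse events named.

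Low power comes from 60 patients, not from the test. Fisher has only about 9% power for 5% versus 15%. No change of test cures that.

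Last, an exact-test fallback is commonly left to a full protocol or analysis plan that is not shown, so its absence alone would be no finding. The point rests on what the article does fix: a chi-square test without condition, and a dropout rule that can remove serious-event patients.

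**Conclusion.** The point holds in a limited form and is worth acting on. The stated rule gives a verdict that can hang on one patient (3 versus 0 against 4 versus 0) or on an unstated variant (0.038 against 0.06 to 0.12). This matters mainly if the pooled rate is below about 17% at 30 per group, or about 21% at 24; both rest on an assumed event rate.

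The larger weakness is imprecision. A tripling from 5% to 15% would be missed about three times in four, and a doubling from 10% to 20% about four times in five. It would be too strong to say that a non-significant result tells nothing: equal low counts exclude differences beyond roughly 11 to 17 points, and power is about 80% for 10% versus 40%.

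The exclusion of patients terminated for a serious adverse event adds a possible bias that no choice of test removes. Its size cannot be worked out from the article.

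**What to change.** Replace the chi-square sentence with a rule along these lines. For all randomised patients, including those who withdraw or whose participation is ended for a serious adverse event, report the number with at least one adverse event in each group, and the risk difference with a 95% score interval (Newcombe or Miettinen-Nurminen), as the main safety result. If a p-value is also given and any expected count is below 5, use a mid-p or Boschloo test, with the choice named in advance. State in the dropout section that its exclusion of data does not apply to the safety analysis.

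The cost is a sentence or two and slightly more analysis work. The intervals will be wide and the change does not raise power, but the reader will see the uncertainty.
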